### Intervention

#### Theory of change.

The intervention is tailored to the unique needs of youth users of tobacco and nicotine products. It has been developed based on state-of-the-art research, insights from experienced Danish cessation counselors, and preferences of young tobacco and nicotine users in partnership with Rygestopkonsulenterne ApS (The smoking cessation consultants), a consulting firm with more than 20 years of experience with tobacco and nicotine cessation counseling (S2).

The intervention targets three focus areas:

A) Training of counselors who assist young smokers and nicotine product users to quitB) Recruitment strategy for youth to tobacco and nicotine cessation servicesC) Cessation course for youth who use tobacco and nicotine products.

It is hypothesized that A) counselors trained through U-Niko will report higher skills and confidence in assisting youth quit attempts than those in control municipalities, B) intervention municipalities will recruit more youth into cessation services than controls, and C) youth participating in the intervention municipalities’ cessation services will have higher abstinence rates after six months than those in control municipalities (Fig 3). Furthermore, it is expected that there will be a synergistic effect by optimizing all three areas at the same time.

**Fig 3 pone.0323514.g003:**
[figure not shown]
The program theory of change in the U-Niko intervention.

### The intervention municipalities

The municipalities will receive the U-Niko intervention, including online and physical materials, for all three focus areas. Table 1 provides an overview of the key elements of the intervention.

**Table 1 pone.0323514.t001:** Overview of the U-Niko intervention content.

Focus area	Key elements
A. Training	• Knowledge of nicotine addiction and relapse prevention • Knowledge and concrete tools to work with youth via behavioral and pedagogical approaches • Knowledge of motivation and ambivalence • Basic knowledge of novel tobacco and nicotine products and their harmful effects • Knowledge of the use of the U-Niko score and how to assess physical dependence • Instructing stress reduction exercises
B. Recruitment	• Step-by-step guidance and tools on how to contact and establish collaborations with youth arenas • Guidance and examples of how to promote the course on tobacco- and nicotine cessation in a motivating way using face-to-face interactions in the youth arena and tools such as videos and posters • Recommendations and examples on how to keep in touch with young people and strengthen their motivation from registration to attendance at the course • Tools and guidance on how to strengthen existing collaboration with a youth arena and how to expand to other arenas year by year
C. Cessation	• Group-based approach, strong focus on community • Commitment to complete cessation from all tobacco and nicotine products • Behavioral counseling • Strengthening of self-efficacy • Focus on a trust-based relationship, to make all participants feel safe • Peer elements and focus on sharing experiences • Understanding of own addiction and tools on how to overcome cravings • Stress reduction exercises • Text messages to S

A, B, C in refers to the three focus areas.

#### A. Training.

Training in the recruitment strategy is delivered through a 1-day course. During training, guidance is offered on how to engage with youth (face-to-face interaction with them in classes or at their workplace, sports clubs, campuses, etc.) and how to motivate them to participate in the course. Videos and posters featuring young peers (role models) sharing their reflections on smoking/nicotine use and desire to quit are provided.

Youth counselor training is delivered through a 2-day course. The youth counselor training program is aimed at both experienced smoking cessation counselors and individuals with a pedagogical background who have never worked with smoking cessation. It focuses on relational and resource-oriented behavioral techniques, knowledge of nicotine addiction, as well as on how to motivate youth to quit tobacco and nicotine and how to prevent relapse. The program focuses on a non-judgmental and supportive approach. Additionally, the training provides a foundational understanding of novel tobacco and nicotine products and their harmful effects.

#### B. Recruitment.

The recruitment strategy is developed as a step-by-step guidance on where to recruit and how to contact youth arenas for recruitment (i.e., schools, workplaces, fitness centers, sports clubs, campuses, barracks, and meeting places for youth), as well as how to encourage them to cooperate. The intervention group will receive free recruitment materials (videos and letters) and guidance on how to recruit in different youth arenas over time.

#### C. Cessation.

The cessation course consists of seven meetings planned over eight weeks. The sessions last between 1.5 hours and 45 minutes. It is advised that approximately twelve young people are recruited for each course established. Participating municipalities can recruit and create as many courses as they wish during the intervention year.

The course is anchored around key constructs from social cognitive theory and posits that learning occurs in a social context with a dynamic and reciprocal interaction of the person, environment, and behavior [21]. Peer elements are used both in recruitment and in group counseling. The approach to young people stems from theories of cognitive behavioral therapy [22], as well as narrative engagement theory [23]. Furthermore, the course is based on the International Child Development Programme (ICDP) and its eight interaction themes as a tool for relationship- and resource-oriented practices [24]. The exercises stem from mindfulness-based cognitive therapy [25] and mindfulness-based stress reduction [26].

As part of the cessation course, a newly developed score (The U-Niko score, validated by 25 young people, S3) is used to measure physical nicotine dependence. The score has been developed because the nationally used Fagerström score is not suitable for youth, since many young people use more than one tobacco and nicotine product, the consumption of e-cigarettes is difficult to measure, and the nicotine content in e-cigarettes and nicotine pouches can vary significantly. The U-Niko score consists of five short questions ranging from to 0–9, with 9 being the highest. A score of ≥ 6 indicates high physical nicotine dependence, suggesting that nicotine patches may be beneficial as a part of the cessation process. For individuals aged 18 + years with a nicotine patch allergy, cytisine is recommended for those with a score of ≥6.

### The control municipalities

The municipalities in the control group will continue their recruitment practices and their youth cessation activities “as usual.” The control municipalities can offer individual or group-based counseling of any duration.

The municipalities are not provided with any information about the intervention or any assistance to improve their recruitment strategies, training of counselors, or youth-oriented cessation activities during the intervention year. However, the control municipalities will be instructed on how to register baseline and follow-up information and will be offered information on how to use the U-Niko score, as the goal is to compare the young participants’ nicotine dependence uniformly in the intervention and control groups. Information on how to use the U-Niko score was delivered via an online meeting in December 2024 (Fig 2).

### Measures and data assessment

The data assessment is ongoing through 2025 and approx. six months into 2026, includes data on the effectiveness of all three focus areas of the U-Niko intervention and involves seven different data sources (Fig 1). Each focus area of the intervention has its own primary outcome.

#### A. Training.

In January 2026, the year after the intervention year, all municipal counselors from both intervention and control municipalities will receive an online survey examining their self-perceived competencies in working with youth tobacco and nicotine cessation using a version of the Short Occupational Self-Efficacy Scale (Short-OSE Scale) adapted to the cessation counseling context and translated into Danish (a scale from to 0–30, 30 being the highest level of perceived self-efficacy) [27].

The primary outcome is *the effect of the training of new youth counselors*, assessed through differences in counselor self-efficacy between the intervention and control municipalities.

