**Methods:**

This protocol describes a two-arm cluster randomized controlled trial of youth aged 16–25 in 55 municipalities in Denmark. Prior to the study a stratified randomization was carried out using the online randomization program Sealed Envelope, allocating 27 municipalities to the U-Niko intervention group and 28 municipalities to the control group (tobacco and nicotine cessation recruitment and counseling as usual). The primary outcomes will measure the effectiveness of all three focus areas in the intervention group compared to the control group: A) the municipal counselors’ self-efficacy in youth cessation counseling, B) the number of recruited youths for cessation counseling, and C) the self-reported 14-day point prevalence of abstinence of youth at six months follow-up. Secondary outcomes are the number of recruited youths in a municipality compared to the previous year, continuous abstinence, and validated 14-day point prevalence of abstinence at six-months follow-up.

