### Data analysis plan

#### A. Training.

A table will present the characteristics of the counselors separately for the intervention and control municipalities, including gender, age, education, years of experience with youth, and experience with tobacco and/or nicotine cessation. The effect of training new youth counselors will be assessed by comparing their self-efficacy scores in the intervention and control municipalities after the intervention year. Because counselors are nested within municipalities, and municipalities are the unit of randomization, a linear mixed-effects model (LMM) with a random intercept for municipalities will be used to account for clustering. The model will be adjusted for counselor characteristics, such as counselor education, years of experience working with youth, and years of experience in tobacco and/or nicotine cessation.

Results from the LMM will be reported as estimated mean differences with 95% confidence intervals (CIs), and a p-value < 0.05 will be considered statistically significant.

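### Primary outcome A is worded for counselor populations that do not match, and its only stated model omits the stratification factors while adjusting for an open list of traits recorded after the intervention

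*Protocol article*

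**What the plan says.** The protocol article describes the counselors behind primary outcome A in three ways.

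- **All municipal counselors.** The abstract names "the municipal counselors’ self-efficacy in youth cessation counseling". Under Measures and data assessment, A. Training, "all municipal counselors from both intervention and control municipalities will receive an online survey" in January 2026.
- **New youth counselors.** The same subsection then defines the outcome as "the effect of the training of new youth counselors". The Data analysis plan, A. Training, repeats this: "The effect of training new youth counselors will be assessed by comparing their self-efficacy scores in the intervention and control municipalities".
- **Trained counselors.** The hypothesis under Theory of change is that "counselors trained through U-Niko will report higher skills and confidence in assisting youth quit attempts than those in control municipalities".

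The intervention section says the youth counselor course is meant for "both experienced smoking cessation counselors and individuals with a pedagogical background who have never worked with smoking cessation".

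On the model, the Data analysis plan gives one linear mixed model with a random intercept for municipality. It continues: "The model will be adjusted for counselor characteristics, such as counselor education, years of experience working with youth", and adds years of experience in cessation work. Additional measures places the recording of counselor education and experience in the post-intervention survey. Randomization says allocation was stratified by municipality size and health cluster. Neither factor is named in the model for outcome A, although municipality size is named in the model for outcome B.

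**The concern.** This is one of three primary outcomes, tested at 0.05. The Discussion plans cost-effectiveness work on whichever focus areas prove effective, so the result for A feeds a decision. If the wording admits more than one population, it admits more than one result.

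The readings differ in kind. Municipalities were randomised, so comparing all their counselors by arm inherits the protection of randomisation, apart from survey non-response. Who attends a course, or who is newly taken on, is settled later by staff and managers. A comparison that picks such people in one arm and sets them against everyone in the other is observational.

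The model raises a second question. Training is open partly to people new to cessation work, so the intervention arm may hold more inexperienced counselors in 2026 than the control arm. Adjusting for experience then estimates something other than the difference between the two workforces, and the plan does not say which of the two is the target.

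**Working it through.** The documents give no sample size, standard deviation, effect size or power for outcome A, so there is no figure to reproduce. The check has two parts.

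**1. The populations side by side (all from the protocol article)**

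| Where | Intervention side | Control side |
|---|---|---|
| Abstract; Measures, A (survey) | all municipal counselors | all municipal counselors |
| Measures, A (outcome); Data analysis plan, A | new youth counselors | not defined |
| Theory of change (hypothesis) | counselors trained through U-Niko | counselors in control municipalities |

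- Trained is not the same as new, because experienced counselors may take the course.
- Trained is not the same as all, because nothing says every counselor in an intervention municipality is trained.
- New is not defined for either arm. The trial gives control municipalities no training help, so U-Niko-trained has no control equivalent.

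**2. What the choices can do to the estimate**

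Every input below is an assumption made for illustration. Only the 27 and 28 municipalities and the 0–30 scale come from the protocol.

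*Dilution.* If a share s of intervention counselors is trained and training adds d points, the all-counselor difference is s × d. With s = 0.5 and d = 3, it is 0.5 × 3 = 1.5 points.

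*Experience mix.* Let training add 1 point on average across the intervention arm, let novices score 3 points lower, and let novices be 40% of the intervention arm and 10% of the control arm.
- Contrast without experience: 1 − 3 × (0.40 − 0.10) = 0.1.
- Contrast at equal experience: 1.
- Simulation (55 municipalities, 4 counselors each, municipality SD 1.5, residual SD 4, 300 trials): 0.04 and 0.95. With a simulation error of about 0.04 on each mean, this agrees with the arithmetic.

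*No training effect at all.* Here there are 27 against 28 municipalities, 4 counselors each, municipality SD 1 and residual SD 4. Experience adds 0.2 points per year up to 15 years, and newcomers occur only in the intervention arm. Newcomers also differ by an unmeasured gap of −2, 0 or +2 points. There were 300 trials per setting, with least squares and cluster-robust errors standing in for the mixed model.

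| Newcomers | Gap | Without experience | With experience | Adjusted test rejects |
|---|---|---|---|---|
| 25% | −2 | −0.90 | −0.45 | 12% |
| 25% | 0 | −0.38 | −0.05 | 6% |
| 25% | +2 | +0.11 | +0.32 | 9% |
| 50% | −2 | −1.78 | −0.78 | 23% |
| 50% | 0 | −0.78 | −0.10 | 6% |
| 50% | +2 | +0.19 | +0.58 | 17% |

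With no newcomers both contrasts are about 0 and the adjusted test rejects in 6–9% of trials. Adjustment removes nearly all of the shift when measured experience explains why newcomers differ, and leaves part of it when it does not. The column without experience is not an error either: it is the difference between the two workforces, which is real under these assumptions.

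**The case against.** The strongest reply is that the operational text points to one population. The survey frame covers everyone, the abstract agrees, the model nests counselors in randomised municipalities, and no trained-only subset is planned. The phrase about new counselors may be only a name for the focus-area A effect, parallel to the names used for recruitment and cessation. A formal analysis set may also stand in a plan not shown. This makes the all-counselor reading the likely intention. It does not remove the conflict, because the Data analysis plan itself ties the compared scores to new youth counselors.

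A reader might infer more than the documents support:

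- *That control municipalities have no new or trained counselors.* The article says only that the trial gives them no help. It also reports that 15 of 28 received Health Authority funding for this work, so they may well have taken on or trained staff.
- *That the intervention changes the workforce.* This is an inference from whom the course is open to. No change is stated or quantified.
- *That the adjusted model is invalid because its covariates are post-randomisation.* They are recorded late, but a person's education and earlier experience mostly predate a 2-day course. If the target is the effect of training, the adjusted model can do better: it gave 0.95 against an assumed effect of 1, where the unadjusted contrast gave 0.04. It was also nearer zero in four of the six no-effect settings above.
- *That the analysis set should be counselors who saw youth in 2025.* That set is selected on activity which outcome B expects the intervention to change. The existing survey frame is the less selected one.

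**Conclusion.** The point holds as one of definition and specification. The article words primary outcome A for populations that do not match, and a literal reading permits a contrast that randomisation does not protect. The only stated model leaves out both stratification factors, has an open covariate list, and does not say whether it targets the workforce effect or the effect at equal experience.

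Whether this changes the result depends on how many intervention counselors are untrained and how far experience differs between arms. Under the assumptions above, the choice of model alone moves the estimate between about 0.1 and about 1 point, and counting untrained staff halves a 3-point effect. These figures show that the choice can matter. They do not predict this trial's result, and the documents do not allow the size or direction of any shift to be determined. The adjusted model is not shown to be wrong, only unlabelled. The correction should be made before the survey data are analysed.

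**What to change.** 1. In Theory of change, Measures A and Data analysis plan A, state that the primary analysis set is all municipal counselors surveyed in both arms. Analyse them by the randomised arm of their municipality, whether or not they were trained and whether or not they counselled youth in 2025.
2. Include municipality size and health cluster in the mixed model.
3. Replace the open list of counselor traits with a closed one.
4. Report the arm contrast without and with counselor education and experience. Label them the workforce effect and the effect at equal experience, and name one in advance as primary.
5. Label any trained-only comparison as supportive and non-randomised.

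The cost is a few sentences and one extra model. The downside is that the all-counselor contrast may be smaller where untrained or novice staff are included.

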#### B. Recruitment.

Data on the number of recruited youths will be registered in STOPbasen. The primary outcome is t*he effect of the recruitment strategy,* which will be assessed by comparing the number of recruited youth participants in the intervention municipalities with the control municipalities.

The secondary outcome is the *change in the number of youth recruited* for cessation activities in the intervention group between the intervention year 2025 and the previous year 2024

#### C. Cessation.

At the first cessation session, all participants in both the intervention and control municipalities will complete a baseline questionnaire on contact information, personal characteristics, information on tobacco and/or nicotine use, and the U-Niko score. The baseline questionnaire also contains a consent form for participation in the study. The baseline questionnaire will be registered in STOPbasen.

Further, the young participants in the intervention group will be invited to answer a short online survey on their experiences with the intervention after the course has ended (4 weeks post-target quit date), regardless of their tobacco and nicotine status.

Six months after the targeted quit date, all participants (in both the intervention and control groups) will be contacted by phone to examine the long-term effects of the cessation offer. A research assistant will contact the participants multiple times by phone and send text messages to decrease the number of missing values at follow-up.

All participants will be informed that each completed questionnaire (baseline survey, post-intervention survey (only intervention group), and six-month follow-up survey) will be entered into a raffle with the chance to win a gift certificate worth 1000 DKK (~134 euros/139 USD). In total, six participants from the intervention municipalities and four from the control municipalities will be drawn to win.

Participants who report being tobacco- and nicotine-free at the six-month follow-up will be invited to undergo a saliva cotinine test to validate their abstinence. The saliva test will be mailed to each participant who has agreed to participate and will be conducted via an online interview using Teams. The participant will take the test and show the answer to the research staff during the online meeting, discard the test, and receive a gift certificate for 300 DKK (~40 euros/42 USD), regardless of the outcome of the validation test.

The primary outcome is *the effect of the cessation course,* which will be measured using *long-term self-reported PPA* (not using any tobacco or nicotine product in the last 14 days) six months after the targeted quit date in the intervention municipalities compared with the control municipalities. To assess this, participants will be asked, “Have you used any tobacco or nicotine products in the last 14 days?” (Yes/No).

The secondary outcomes are *short-term self-reported abstinence* (i.e., at the end of the cessation course/counseling), *continuous self-reported abstinence* (from targeted quit date to six-month follow-up), and v*alidated PPA,* which will be assessed in all participants who report being tobacco and nicotine abstinent at the six-month follow-up and agree to participate in the cotinine validation process.

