#### C. Cessation.

The analyses of the primary outcome on self-reported 14-days PPA at six months follow-up will follow the intention-to-treat (ITT) principle, assuming that all non-respondents are currently smoking or using nicotine. Data will be analyzed using a generalized linear mixed model (GLMM) to account for clustering, recognizing that youth participants within the same municipality may be more similar to each other than to participants from other municipalities. Results will be presented in a table as odds ratios (ORs) for 14-day PPA at six months after the targeted quit date, with corresponding 95% CIs. A p-value < 0.05 will be considered statistically significant.

Secondary outcomes, including short-term self-reported abstinence, continuous self-reported abstinence, and validated 14-days PPA at six months follow-up, will be analyzed using the same GLMM approach as for the primary outcome and presented in tables as ORs with corresponding 95% CIs. In addition, a table will present and compare the baseline characteristics of all youth participants between the intervention and control groups, including age, educational level, type of nicotine product used, and follow-up participation rates.

Given the high degree of data completeness in STOPbasenwe intend to employ a complete case analysis, excluding patients with any missing values in the included variables from the analysis (listwise deletion). Consequently, a sensitivity analysis using an as-observed approach will be conducted, including only participants with a valid follow-up. Sensitivity analyses will be performed using the final adjusted model from the main analyses. This approach builds on the assumption that data is Missing Completely At Random (MCAR). However, when it comes to smoking status, data are more likely to be Missing Not At Random (MNAR). Therefore, if necessary, considering the number of missing values and loss to follow-up, a sensitivity analysis using a chained multiple imputation model will be conducted based on the final adjusted model in the main analyses.

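### The short-term abstinence odds ratio compares a point about 4 weeks after the quit date in one arm with an unfixed point in the other, so it mixes treatment effect with time since quitting

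*Protocol article*

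**What the plan says.** All references are to the protocol article.

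- **Definition.** Under Measures and data assessment, C. Cessation, short-term self-reported abstinence is a secondary outcome, timed "i.e., at the end of the cessation course/counseling". The definition gives neither a number of weeks from the quit date nor an abstinence window.
- **Analysis.** The Data analysis plan, C. Cessation, names it among the outcomes for comparison: "Secondary outcomes, including short-term self-reported abstinence, continuous self-reported abstinence, and validated 14-days PPA at six months follow-up" are to be modelled as the primary outcome is and shown as odds ratios with 95% confidence intervals.
- **Intervention arm.** The Intervention section, C. Cessation, plans seven meetings over eight weeks. The measures section mentions a "short online survey on their experiences with the intervention after the course has ended (4 weeks post-target quit date"), which places the end of the course at about 4 weeks after the quit date.
- **Control arm.** Under The control municipalities: "The control municipalities can offer individual or group-based counseling of any duration".
- **Six-month outcomes, for contrast.** Participants in both arms are telephoned six months after the target quit date, so time since quitting is the same in both arms.

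**The concern.** Whether a young person is abstinent depends strongly on how long ago the quit attempt began. A comparison at the end of support is a same-time comparison only if support ends equally long after the quit date in both arms. Here one arm has a set programme and the other has usual practice with no set length. If control counseling tends to be short, controls are assessed early, when fewer have relapsed, and the intervention looks worse than it is. If control counseling tends to be long, the reverse holds. A reader of the results table would see an odds ratio from the same model as the primary outcome and would probably take it as an early treatment effect. Part or all of it could be timing.

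**Working it through.** **Step 1. Time of assessment, side by side.**

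| | Intervention | Control |
|---|---|---|
| Support | Seven meetings over eight weeks | Individual or group, any duration |
| End of support, from target quit date | About 4 weeks | Not fixed |
| Six-month contact | Fixed from quit date | Fixed from quit date |

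The article gives no expected rate for short-term abstinence, so there is no planned figure to reproduce. The rest is an illustration of size.

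**Step 2. Inputs.**

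- Week-26 abstinence: 23% in both arms. This is the control rate in Sample size calculations, applied to both arms so that the true effect is nil.
- Week-4 abstinence: 50%, assumed, with a range of 40% to 60%. The article gives no value.
- Relapse: exponential, identical in both arms, assumed.
- Intervention arm assessed at week 4; control arm at week t, with t = 1, 2, 4, 8 or 12, assumed.

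**Step 3. Formulas.** With s4 the week-4 proportion:

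- weekly relapse rate λ = ln(s4 / 0.23) / 22
- control proportion at week t: s(t) = s4 × exp(−λ(t − 4))
- odds ratio = [s4 / (1 − s4)] / [s(t) / (1 − s(t))]

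**Step 4. Numbers for s4 = 50%.** λ = ln(0.50/0.23)/22 = 0.777/22 = 0.0353.

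- Week 1: s = 0.50 × exp(0.0353 × 3) = 0.556; odds ratio = 1/(0.556/0.444) = 0.80.
- Week 12: s = 0.50 × exp(−0.0353 × 8) = 0.377; odds ratio = 1/(0.377/0.623) = 1.65.

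**Step 5. Odds ratio with no true effect, by the week in which control counseling ends.**

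| Abstinent at week 4 | Week 1 | Week 2 | Week 4 | Week 8 | Week 12 |
|---|---|---|---|---|---|
| 40% | 0.88 | 0.92 | 1.00 | 1.18 | 1.37 |
| 50% | 0.80 | 0.86 | 1.00 | 1.30 | 1.65 |
| 60% | 0.69 | 0.79 | 1.00 | 1.48 | 2.04 |

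**Step 6. A yardstick.** The planned six-month effect, 34% against 23%, is an odds ratio of (0.34/0.66)/(0.23/0.77) = 0.515/0.299 = 1.72. In the middle row, timing alone at week 12 gives 1.65, close to the effect that the trial is designed to detect at six months.

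**Limits.** The illustration puts all controls at one end week, whereas real controls would be spread over several. It ignores clustering. The curve before week 4 is an extrapolation.

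**The case against.** **End of support is a legitimate endpoint.** In a field trial against usual practice, comparing each arm when its own support ends is a coherent pragmatic question. This stands in part. Such a comparison can be described, but it answers a different question from a same-time comparison. The article does not present it as such, and gives it the same model and effect measure as an outcome that is anchored in time.

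**Control counseling may end near week 4 anyway.** It may, and the bias would then vanish. The article does not show that control timing differs, only that nothing fixes it.

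**A reader might infer that controls are never assessed.** The only post-course contact described is a "post-intervention survey (only intervention group"). Primary-outcome non-respondents are handled by "assuming that all non-respondents are currently smoking or using nicotine", so one could conclude that all controls would be recorded as using and their abstinence as 0%. The documents do not support this. That survey is described as being about experiences with the intervention, and nothing says that it measures short-term abstinence. Follow-up assessments run through the municipalities with STOPbasen, and the article counts seven data sources and points to a figure not shown here. A common source may therefore exist. The non-respondent rule is also stated for the primary outcome; it is not said to cover youths who were never asked.

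**A reader might also infer that the extra survey and raffle entry bias the six-month primary outcome,** by raising response in one arm only. This is speculative. The six-month contact procedure is the same in both arms. Follow-up participation rates will be tabulated by arm, and an as-observed sensitivity analysis is planned. No document gives a figure for any difference in response. The prize numbers, six over three questionnaires and four over two, are also consistent with two prizes per questionnaire in each arm.

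**Conclusion.** The point holds in this form: the plan commits short-term abstinence to a between-arm odds ratio at a moment tied to about 4 weeks after the quit date in one arm and to no set time in the other. The estimate therefore mixes effect with time since quitting, even if the same database supplies both arms. The bias can go either way. With no true effect, the odds ratio runs from about 0.80 to 1.65 for control counseling ending 1 to 12 weeks after the quit date, and from 0.69 to 2.04 when the assumed week-4 rate is varied from 40% to 60%. It is 1.00 if control counseling ends at week 4.

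These sizes rest on the assumed week-4 rates, the exponential shape and the single control end week. That timing enters the comparison rests only on the article's own text and on abstinence changing with time since quitting. The matter is confined to one secondary outcome. The documents do not show that controls go unmeasured or that the primary outcome is biased.

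**What to change.** 1. Define short-term abstinence at one fixed time from the target quit date in both arms, for example 4 weeks, as is already done at six months.
2. Use the same question, a stated abstinence window and the same source in both arms: either one short message to every participant, or one STOPbasen status item accepted within a common window. The second option also serves youths who are already past the chosen time, if the item was recorded.
3. If neither is possible, drop the between-arm odds ratio. Report the outcome descriptively by arm, together with the distribution of time from the quit date to assessment.
4. Reconcile the Abstract, whose list of secondary outcomes omits short-term abstinence, with the measures section and the analysis plan.

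**Cost.** One extra brief contact for control participants, or the loss of one secondary odds ratio. The primary outcome, sample size and six-month follow-up stay as they are.
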